#### Intervention fidelity

To ensure good adherence and competence to the FBC intervention, all sites will conduct regular supervision of therapists, in which cases will be discussed and audio/video reviewed. 5 % of all recorded sessions across all sites will be rated by blind independent raters against relevant fidelity and competence criteria, selected at random throughout the course of therapy (with an emphasis on selecting earlier rather than later sessions). All therapists will complete an initial intensive 4-day training in FBC, led by an experienced BA therapist (ERW) and will have to demonstrate competence and fidelity in an observer-rated role-play to receive certification to deliver therapy for the trial. A therapy template form will also guide therapists in session delivery, recording what participants received and guide supervision. A follow-up 2-days training session involving all therapists will be performed. Adherence to the manuals will be rated by using a checklist to assess the presence of key therapy components in general and for each specific session. Competence will be rated by using an adjusted Cognitive Therapy Rating Scale for the FBC intervention. Kappa statistics on inter-rater reliability will be reported.

### Outcomes

#### Primary outcome

The primary outcome of this prevention trial will be the 12-month onset of an episode of MDD, defined according to the standard psychiatric Diagnostic and Statistical Manual of Mental Disorders, Fourth Edition (DSM-IV) criteria using the Depression section of the MINI 5.0 at 3, 6, and 12 months. The MINI 5.0 is a brief standardized diagnostic interview used to assess disorders described in the DSM-IV [73].

#### Secondary outcomes

Secondary outcomes will be assessed at baseline, 3, 6, and 12 months after start of study by using the following measures: PHQ-9 [38] and the self-rating version of the Inventory of Depressive Symptomatology (IDS30-SR) [64] will be used to assess depressive symptoms. The Generalized Anxiety Disorder-7 (GAD-7) questionnaire will be used to assess anxiety symptoms [74]. Health-related quality of life will be assessed by the EuroQol instrument EQ-5D-5 L (EuroQol Group, 1990). Food-related behavior will be assessed by the Three-factor Eating Questionnaire (TFEQ-R18) [36], and a MooDFOOD project developed Food Behavior Questionnaire that assesses meal pattern, snacking behavior, and other food-related behaviors in the past two weeks, such as mindful eating, cooking and shopping skills. Food intake will be assessed by the GA2LEN-FFQ questionnaire [24]. Physical activity and sedentary behaviour will be assessed by the Short Questionnaire to Assess Health-Enhancing Physical Activity (SQUASH) [77] and the Sedentary Behavior Questionnaire (SBQ) [63]. Body weight perception will be assessed by the Stunkard figure rating scale [75].

Mediating/moderating variables: Some secondary outcomes (food intake and food-related behavior, body image perception, and psychological eating behavior) will also be considered as mediating variables to explain impact on the primary outcome. Additional mediating mechanisms will also be assessed: Adherence to pills will be assessed with an adapted version of the Morisky Adherence Scale, a structured four-item self-reported adherence measure [51]; Anthropometry (measured height, body weight, waist circumference according to standardized measurement protocols and calculated BMI); Body composition (fat mass, fat-free mass and percentage body fat) will be accurately assessed using whole body air-displacement plethysmography (BodPod) in participants from one site (Exeter); and blood pressure. Patterns of behavior will be assessed by the Behavioral Activation for Depression Scale (BADS) [35] a 25-item questionnaire measuring changes in avoidance and activation over the course of behavioral activation, and the Self-Report Behavioral Automaticity Index (SRBAI) [25] adapted to measure changes in patient-identified healthy and unhealthy mood and food-related habits. Somatic health status will also be assessed in terms of self-report of somatic/chronic diseases, smoking, alcohol consumption and medication/supplements use at 6 and 12 months.

In a subsample of trial participants, blood samples will be collected at baseline, and after 6 and 12 months to measure blood levels of the nutrients provided with the multi-nutrient supplements, as a manipulation check for adherence to the multinutrient supplements/diet change.

The following descriptive variables and potential moderating variables will be assessed only at baseline: country, age, gender, educational level, family’s medical history, household income, earlier psychiatric history and somatic health status participants through self-report of somatic diseases.

### Sample size

Effective preventive interventions in high-risk groups are found to reduce the onset of depression by as much as 25–50 % [7]. We have therefore powered this trial at the conservative end of this range, by assuming a difference of 33 % in the 12-month cumulative incidence rate of DSM-IV episodes of MDD between the presence of an active condition (estimated 12-month cumulative incidence of MDD 20 %) versus its absence (estimated 12-month cumulative incidence of MDD 30 %) (i.e., FBC versus no FBC; multinutrient supplement versus placebo). The 2×2 factorial design is efficient for sample size and power and enables us to test for potential synergistic interactions between interventions [13, 14]. Assuming a difference between an active condition (20 % incidence of MDD) and a control condition (30 % incidence of MDD), 392 participants would be needed to evaluate the main effect of each nutritional intervention assuming a 2-sided test at α = .05 and a power of (1 − β) = 0.90. This means that 196 participants in each of the four cells would be needed. Assuming a follow-up attrition rate of 22 %, a total of 250 participants per cell would be sufficient. A reduction in sample size to 147 participants in each cell would reduce the power to detect an effect of this magnitude to 80 % power.

### Statistical analysis plan

Statistical reporting will follow the CONSORT standards [72]. Missing data will be inspected and handled via full information maximum likelihood (FIML) or multiple imputations (MI) as appropriate. The primary analyses will be Intention-To-Treat (ITT) analyses [78]. Subsequent analyses will use the Complier Average Causal Effect (CACE) analysis [3, 20] to provide an estimate of a treatment effect taking into account adherence and compliance with the treatment, whilst retaining the benefits of randomization.

Following the 2×2 factorial design of the trial, we will test for the effects of the two nutritional strategies separately as well as combined using logistic regression models for the dichotomous primary outcome (12-month cumulative incidence of episodes of major depressive disorder). The secondary outcomes will be examined using mixed models or generalized estimating equations (GEE) to assess the longitudinal change in depressive symptoms, and other secondary outcomes. We will adjust the analyses for site and history of MDD to account for the two stratification variables used in the randomization [34]. The results from the trial will be prepared as comparative summary statistics with 95 % confidence intervals. *P*-values <0.05 will be considered statistically significant.

For the secondary objectives, we will conduct mediation analyses to gain insight into mechanisms that could explain the potential effect of the nutritional interventions on depression. We will use modern causal inference methods using parametric regression models to assess mediation effects [21]. This involves using parametric regression models to test for mediation of the dietary interventions on depression through changes in the mediating variables. In addition, we will investigate potential moderation of the nutritional strategies on depression by site, age, sex, educational level, comorbid illness, initial BMI, and depression history.

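### The plan does not say how each secondary scale's baseline value enters the longitudinal model; an ordinary reading would widen the confidence intervals unnecessarily

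*Protocol article*

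**What the plan says.** The Statistical analysis plan section of the protocol article examines the secondary outcomes "using mixed models or generalized estimating equations (GEE) to assess the longitudinal change in depressive symptoms, and other secondary outcomes". On covariates it says: "We will adjust the analyses for site and history of MDD to account for the two stratification variables used in the randomization". The reason given is the stratified randomisation. No outcome's baseline value is mentioned, and nothing says that it is left out.

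The Secondary outcomes section gives the schedule: "Secondary outcomes will be assessed at baseline, 3, 6, and 12 months after start of study". Table 2 agrees, with a baseline tick for every self-administered questionnaire. The section on consent, baseline and follow-up assessments places randomisation after the baseline measurement, so the arms differ at baseline by chance alone.

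On missing data the plan says: "Missing data will be inspected and handled via full information maximum likelihood (FIML) or multiple imputations (MI) as appropriate". It states no standard deviation, correlation or target precision for any secondary scale.

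**The concern.** Two common ways of assessing change over time treat the baseline as an outcome. One is a group-by-time model with a separate baseline mean in each arm; the other is a change score. Both estimate a difference in change, so the measurement noise and any chance imbalance at baseline go into the treatment contrast. Adjusting for site and MDD history does not replace the baseline PHQ-9, IDS-SR30 or GAD-7 value.

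Because baseline precedes randomisation, its mean may properly be set equal across arms, or its value entered as a covariate. Either route removes the avoidable noise. At stake is the width of the 95% confidence intervals for symptoms, anxiety, quality of life and the other secondary scales, each of which is to be judged against P < 0.05.

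**Working it through.** **The plan's own figure.** The only sample-size calculation is for the primary outcome: "Assuming a difference between an active condition (20 % incidence of MDD) and a control condition (30 % incidence of MDD), 392 participants would be needed", "assuming a 2-sided test at α = .05 and a power of (1 − β) = 0.90". With pooled variance and no continuity correction, n = [1.96·√(2·0.25·0.75) + 1.2816·√(0.3·0.7 + 0.2·0.8)]² / 0.10² = 392 per factor level, which reproduces the figure. That is 196 per cell. With 22% attrition, 250 per cell leaves 250 × 0.78 = 195 per cell, or 390 per factor level. These numbers serve below only as the n for a secondary contrast.

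**Assumptions not in the article.** The outcome has SD 1 at every visit. r is the correlation between baseline and one follow-up visit, after allowing for site and MDD history. There are no missing data.

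**Per-arm variance at one follow-up visit.**
- Difference in change: 2(1 − r).
- Baseline-adjusted or baseline-constrained: 1 − r².
- Proportional reduction: 1 − (1 − r²)/[2(1 − r)] = (1 − r)/2.

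| r (assumed) | Change | Adjusted | Variance cut | SE cut |
|---|---|---|---|---|
| 0.2 | 1.60 | 0.96 | 40% | 22.5% |
| 0.4 | 1.20 | 0.84 | 30% | 16.3% |
| 0.5 | 1.00 | 0.75 | 25% | 13.4% |
| 0.6 | 0.80 | 0.64 | 20% | 10.6% |
| 0.7 | 0.60 | 0.51 | 15% | 7.8% |
| 0.9 | 0.20 | 0.19 | 5% | 2.5% |

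If the baseline SD s₀ differs from the follow-up SD s₁, the variance saved is s₀² + s₁² − 2r·s₀·s₁ − s₁²(1 − r²) = (s₀ − r·s₁)². This is never negative, so the direction does not depend on equal variances, although the percentages do.

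**Check with the full repeated-measures model.** Generalised least squares was run for four visits, compound symmetry and 390 per factor level, on the 12-month contrast. At r = 0.5 the variance is 0.005128 with free baseline means and 0.003846 with a common baseline mean, a 25% cut. At r = 0.4, 0.6 and 0.7 the cuts are 30%, 20% and 15%, as in the table.

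**Average of the three follow-ups, compound symmetry.** The variances are (1 + 2r)/3 + 1 − 2r for change and (1 + 2r)/3 − r² adjusted. The cut is 45% at r = 0.4, 37.5% at r = 0.5 and 22.5% at r = 0.7.

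**What this means for power.** Take 392 per factor level and an assumed effect of 0.2 SD. At r = 0.5 the SEs are √(2·1.00/392) = 0.0714 and √(2·0.75/392) = 0.0619. Power, Φ(0.2/SE − 1.96), is 80% against 90%. At r = 0.4 it is 72% against 86%; at r = 0.7, 95% against 97.5%. With 390 per level and r = 0.5, the difference detectable with 90% power falls from 0.232 SD to 0.201 SD.

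**The case against.** The strongest reply is that the article does not choose the inefficient model. It names neither a change score nor free baseline means, and the adjustment sentence serves to honour the stratification, not to close the covariate list. A mixed model with a common baseline mean is also a mixed model of longitudinal change, fits the FIML option, and loses nothing. How baseline enters such a model is the kind of detail a condensed article often leaves to a full analysis plan, which is not shown here.

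Most of this stands. A reader might infer that the plan adjusts for site and MDD history alone and discards each baseline value. The text does not support that: it is silent on the point. A reader might also take 15–30% as the trial's actual loss. That range is a variance at one visit, depends on an assumed r of 0.4 to 0.7, and arises only under the unconstrained or change-score reading. At the upper end of r the gain is small.

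What remains is that the article does state a target, change, and does name adjustment variables. An analyst following those words literally could well fit the less precise model.

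**Conclusion.** The point holds as a free improvement to the precision of the secondary outcomes, not as an error in the plan. If the secondary models are run with free baseline means or change scores, the variance of the treatment contrast at one visit is larger than it need be. Baseline adjustment would cut it by (1 − r)/2, with the sizes set out above. These rest on equal variances over time and on an r that the article does not supply.

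It would be wrong to go further and call the estimates biased. Over randomisation the difference in change is unbiased. A chance baseline imbalance shifts a particular estimate, but the standard error already allows for that. The logistic analysis of 12-month MDD incidence is not touched.

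**What to change.** Add one sentence to the analysis of secondary outcomes. Each outcome is analysed with its baseline value either as a covariate for the 3-, 6- and 12-month values, or in the outcome vector of a likelihood-based mixed model with one common baseline mean across the four randomised cells; site and history of MDD stay in the model. If GEE is chosen, the covariate form is the safer one: under an independence working correlation, a common baseline mean passes no information to the later visits.

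The cost is that sentence. The baseline data are already scheduled, and neither the sample size nor the primary analysis changes. The article reports that recruitment was still under way, so the wording could be settled before any unblinded analysis. If a full analysis plan already says this, confirming it is enough.

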### Eligibility criteria

Inclusion criteria for the study are that participants will be adults aged 18 to 75 years old, meet criteria for being overweight or obese (body mass index (BMI) between 25–40 kg/m^2^) and report subsyndromal symptoms of depression as operationalized by a Patient Health Questionnaire (PHQ-9) score of at least 5. Overweight individuals with elevated symptoms of depression will be recruited because both of these variables increase vulnerability for subsequent MDD episodes. This will increase the potential base rate of incidence of depression during the follow-up period, and, thereby, the sensitivity of the prevention study. Furthermore, a nutritional intervention has greater scope to be beneficial in this group, as both obesity and depression are associated with unhealthy diet and unhealthy food-related behaviors.

Because this is a prevention trial, rather than an acute treatment trial, participants will be excluded at baseline if presenting with a current episode of (including the past 6 months) MDD (according to psychiatric DSM-IV criteria), as determined in a structured MINI International Neuropsychiatric Interview 5.0 (MINI 5.0). Other exclusion criteria include: Current (in past 6 months) use of antidepressant drugs or psychological interventions; Current eating disorder; History of psychosis, bipolar disorder, substance dependence or other severe, psychiatric disorder that requires specialized clinical attention; History of or planned bariatric surgery; Currently pregnant or breastfeeding; Current severe, life-threatening physical disease (assessed using self-report); Severe cognitive impairment sufficient to limit the conduct of the study as assessed through research staff evaluation of participant’s ability to complete the screening instruments in an adequate manner; Currently adhering to supervised behavioral interventions that interfere with MooDFOOD prevention trial interventions; Unwilling to stop using specific dietary supplements that are used or are competing with the MooDFOOD prevention trial multi-nutrient intervention.

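### The primary logistic model adjusts for site and MDD history only; adding the baseline symptom score already collected would give a modest gain in precision at little cost

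*Protocol article*

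**What the plan says.** Under Statistical analysis plan, the primary outcome (12-month cumulative incidence of MDD, yes or no) is analysed by logistic regression. The covariates are given with their reason: "We will adjust the analyses for site and history of MDD to account for the two stratification variables used in the randomization". No other covariate is named for the primary model. Severity is not a stratification factor (Randomization, allocation and masking), and it is not in the list of moderators at the end of the analysis section.

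The Eligibility criteria explain that overweight people with elevated symptoms are recruited "because both of these variables increase vulnerability for subsequent MDD episodes". Under Secondary outcomes, "Secondary outcomes will be assessed at baseline, 3, 6, and 12 months after start of study"; the measures include PHQ-9 and IDS-SR30. Table 2 of the article likewise schedules both at baseline.

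The Sample size section plans for 20% versus 30%, "assuming a 2-sided test at α = .05" and "a power of (1 − β) = 0.90". From this it concludes that "392 participants would be needed to evaluate the main effect of each nutritional intervention", and hence that "196 participants in each of the four cells would be needed".

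**The concern.** The trial selects participants on symptom level because it expects symptom level to predict the endpoint. It measures that level at baseline with two instruments, but the stated primary model does not use it. Lifetime MDD history is in the model, but a yes/no history is not the same as current severity.

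Leaving out a baseline variable that predicts the outcome gives up some power in both main-effect tests. It also leaves any chance difference in baseline severity between the randomised groups in the observed effect. If such a difference is noticed after unblinding, a late adjustment would look data-driven. Recruitment was still under way when the article was written, so the covariate could be named in time.

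**Working it through.** **Inputs from the document.** Two-sided α 0.05; power 0.90; 12-month incidence 30% without and 20% with an active condition; 392 per level of each factor (196 × 4 = 784 analysed); 147 per cell for 80% power.

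**Step 1: reproduce the planned size.** For two proportions with pooled variance under the null and no continuity correction:

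n = [z₀.₉₇₅ √(2 p̄(1 − p̄)) + z₁₋β √(p₁(1 − p₁) + p₂(1 − p₂))]² / (p₁ − p₂)²

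with p̄ = 0.25.

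- 90% power: (1.960 × √0.375 + 1.282 × √0.37)² / 0.01 = (1.2002 + 0.7795)² / 0.01 = 391.9, so 392 per level. This agrees with the article.
- 80% power: the same formula gives 293.2, so 294 = 2 × 147. This also agrees.
- Power at 392 per level is 0.900. The target is met by an unadjusted comparison.

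**Step 2: gain from adding severity.** The document gives no strength of association between severity and MDD onset, so a range is assumed. Setup of the simulation:

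- 784 analysed participants, 392 per level of one factor, 4,000 simulated trials per row.
- Marginal risks held at 30% and 20%.
- Four equal sites with assumed log-odds shifts of −0.3, −0.1, 0.1 and 0.3.
- Lifetime MDD history assumed in 35%, with odds ratio 2.
- Severity assumed standard normal and independent of the other covariates.
- Two-sided Wald test of the treatment coefficient in logistic regression.

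The comparator is the planned model (site and MDD history). The last column converts the two powers to an equivalent sample-size ratio, ((1.96 + z of adjusted power) / (1.96 + z of planned power))².

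| Assumed odds ratio per SD | Power, site + history | Power, severity added | Gain (points) | Sample-size ratio |
|---|---|---|---|---|
| 1.25 | 90.7% | 91.1% | 0.4 | 1.01 |
| 1.5 | 90.8% | 91.3% | 0.5 | 1.02 |
| 1.75 | 90.2% | 91.3% | 1.1 | 1.04 |
| 2.0 | 91.5% | 93.2% | 1.7 | 1.07 |
| 2.5 | 90.4% | 93.8% | 3.4 | 1.15 |

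The ratio in the first row is 1.015 before rounding, so the range is roughly 2% to 15%. The Monte Carlo standard error of each gain is about 0.2 to 0.3 points. With severity unrelated to outcome (odds ratio 1.0), power was 90.5% and 90.6%, so adjustment costs essentially no power if the assumption fails.

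**Step 3: a lower event rate.** With 15% versus 10% (assumed; the same relative reduction), power is about 57% and the gain is 0.2 to 3.1 points over the same odds ratios, with a standard error of up to 0.5. Adjustment would not rescue a trial with too few events.

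**Step 4: chance imbalance.** With 392 per level, the 95% range of the difference in a standardised score is ±1.96 × √(2/392) = ±0.14 SD. An imbalance at that limit moves an unadjusted 10-point risk difference by about 1.0 point at an odds ratio of 1.5 per SD and by about 2.1 points at 2.5. The 95% confidence interval already has a half-width of 1.96 × √(0.37/392) = 6.0 points, and that width includes this source of noise.

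**The case against.** The strongest reply is that nothing here is wrong. Adjusting for the stratification factors is correct practice, and the sentence gives that as its purpose without saying that the list is complete. The full protocol or SAP, which is not shown, may add covariates. Planned power does not depend on the change. All of this stands, and it sets the weight of the point. It does not remove the point: the article names a covariate set, and its own rationale points to one more variable that is already collected.

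Three stronger readings are tempting, and the document supports none of them.

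- *The trial loses substantial power.* A reader might infer this from the absence of an upper PHQ-9 limit, taking baseline risk to vary widely. But the interview excludes MDD now or in the past 6 months, recent antidepressant or psychological treatment is also excluded, and the population is described as subsyndromal. Severity is restricted at both ends, which can weaken its prognostic value. The gain reaches 2 points only if the odds ratio exceeds about 2 per SD.
- *The omission biases the result.* It does not. Randomisation protects the type I error, and chance imbalance is noise that the confidence interval already reflects.
- *The change is free.* Not quite. The odds ratio is non-collapsible, so adding a prognostic covariate changes the target to a different conditional odds ratio, further from 1 and with a larger standard error. Missing baseline scores also need handling.

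**Conclusion.** The point holds as a recommendation of modest weight. The planned primary analysis is valid and its stated 90% power is reproduced without further adjustment. Adding baseline severity would bring about 0.4 to 3.4 power points, or roughly 2% to 15% more effective participants, for odds ratios of 1.25 to 2.5 per SD.

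That range is an assumption, as are the normal severity score, the prevalence and effect of MDD history, the site effects, and the independence of severity from MDD history. If severity and history are correlated, part of the gain is already captured by the planned model. What rests on the document alone is that the named covariates are site and MDD history, that two severity scores are available at baseline, and that the article treats symptoms as a risk factor for the endpoint.

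**What to change.** Before unblinding, prespecify one baseline severity score, IDS-SR30 or PHQ-9, as a continuous covariate in the primary logistic model, alongside site and MDD history. From that model, report standardised 12-month risks by level of each factor, with the risk difference and risk ratio and their 95% confidence intervals, so that the result stays comparable with the 30% versus 20% planning figures. State that the odds ratio from the model is conditional on the covariates.

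The cost is small: a few sentences of analysis text and a standardisation step. No new data are needed. Missing baseline scores can be handled under the FIML or multiple imputation already planned. The sample size need not change.
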